## Abstract

**Background:**

Work-related injuries of the shoulder complex represent a challenge for clinicians because of the large variety of clinical entities involved and the broad anatomic structures that can be affected. Furthermore, commonly performed orthopedic tests have demonstrated limited accuracy for diagnosing the injury despite considerable research efforts. The aim of this study protocol is therefore to describe a comprehensive approach integrating both a clinical- and functional status-based pathology and an adapted rehabilitation prescription.

**Methods/Design:**

A longitudinal cohort study will be performed at the Department of Rehabilitation and Medical Assistance of a mutual insurance society for work-related injury management in Spain (Mutua Navarra, Pamplona, Navarra Spain). Patients will be attended by an occupational physician who specializes in work-related injuries and is part of the project team that will systematically visit all the participants. After the medical diagnosis and any requested supplementary evaluations (i.e., radiological examinations), the patients will be referred to the rehabilitation service. Before the physiotherapeutic rehabilitation program is initiated, the patients will undergo a comprehensive functional screening at the biomechanics laboratory. Using a decision-making scheme, the identified functional deficits will be used to customize the individual rehabilitation plan.

**Discussion:**

The proposed objective criteria-based shoulder diagnosis and rehabilitation model could be a new effective strategy for minimizing the time required to regain functional capacity and recover from symptoms among patients with work-related shoulder injuries.

**Trial registration:**

The study protocol has been registered on Clinical Trials.gov as NCT02732002 (April 10^th^ 2016).

**Electronic supplementary material:**

The online version of this article (doi:10.1186/s12891-017-1435-2) contains supplementary material, which is available to authorized users.

## Background

Persistent shoulder pain and functional impairments are common among patients with shoulder injuries, accounting for 5% of all medical practice visits [1]. As reported by Ginn et al. 2005 [2], the shoulder is the fourth most common site of musculoskeletal pain reported by patients visiting physicians or physical therapists, exceeded only by the neck, knee and back regions. Causal relationships were recently reported by B Larsson et al. 2007 [3] between forceful exertions, a high level of static contractions, prolonged static loads, extreme postures, and combinations thereof and work-related disorders of the shoulder. Stressful working postures, e.g., working with the arms above shoulder height, have also been shown to increase the risk of long-term sickness absence in the general working population [4].

Shoulder pain can arise from different anatomical structures or a combination of several structures. Thus, subacromial or external impingement syndrome (SIS), rotator cuff pathology, superior labrum anterior posterior (SLAP) injury and glenohumeral (GH) ligament insufficiency are the most frequently cited anatomical pain-eliciting structures [5]. Other authors have described other clinical entities related to shoulder pathology, such as the so-called internal impingement syndrome and scapular dysfunction syndrome [6, 7]. Internal impingement syndrome is described as a compromise of the supraspinatus tendon against the greater tubercle of the humerus and the postero-superior glenoid rim [6]. Scapular dysfunction is defined as an alteration of scapular kinematics concomitant with rotator cuff impingement or disease and is characterized by a lack of posterior tilting, upward rotation and increased internal rotation or medial rotation of the scapula [7].

Several orthopedic tests are commonly performed to identify the clinical entity causing the pain. In short, these tests involve moving the affected arm into different positions, which are believed to irritate different shoulder structures [3, 6]. Depending on which testing position reproduces the greatest pain level, a clinical diagnosis is based on the link between the reproduced arm posture and the biological structure being stressed. For a more comprehensive explanation of the most frequently utilized orthopedic tests in the practical setting, the reader is referred to the following reports [3, 6, 8]. However, there is a lack of isolated orthopedic tests with sufficient sensitivity and specificity to diagnose and justify the commonly observed clusters of symptoms in many shoulder patients [6, 9]. Various authors have therefore focused their research on this issue, concluding that clustering orthopedic tests in relation to isolated clinical entities would improve their diagnostic accuracy [9, 10].

Several biomechanical models of shoulder function in the presence or absence of shoulder injury [11–16] have been developed. However, less is known regarding the standard of reference for the rehabilitation process. In this context, exercise therapy represents the most effective treatment for shoulder injury rehabilitation in terms of both symptomatic relief and function restoration [15–18]. In fact, numerous studies have assessed the effectiveness of exercise therapy versus other treatment modalities and have described the biomechanical (kinetic description) or neuromuscular (EMG activity) rationale for treating different causes of shoulder pain. For work-related shoulder pain, strength training in particular has demonstrated promising results for reducing pain and improving function [19, 20].

However, in the authors’ opinion, a comprehensive rehabilitation model for shoulder injuries that integrates the clinical entity and functional status and provides an individualized exercise rehabilitation program based on all the information obtained from both clinical and functional examinations is lacking. The purpose of the present study protocol is therefore to establish a comprehensive clinical model for shoulder injury management that integrates both clinical and biomechanical assessments and targets individual deficits in the posterior rehabilitation program. The present study protocol will be implemented by a non-lucrative public medical insurance corporation that functions as a satellite of the national public health system in Spain.

If our hypothesis is correct, an objective criteria-based rehabilitation algorithm (OCBRA) for rehabilitation could become a new effective strategy for improving functional capacity and symptom recovery among patients with shoulder injuries. This intervention is designed to improve the rate of complete return to previous activity levels, for which a concise clinical diagnosis and functional status picture seems imperative.

## Methods/Design

### Background

#### Study design and setting

This longitudinal cohort study with a historical clinical cohort serving as control group will be conducted at the Department of Rehabilitation and Medical Assistance of a mutual insurance society for work-related injury management in Spain (Mutua Navarra, Pamplona, Spain). The patients will be attended by a physician trained in the protocol implemented during this research. Following medical diagnosis and supplementary evaluations when requested (i.e., radiological examination), the patients will be referred to the rehabilitation service. Before initiating the physiotherapeutic rehabilitation program, the patients will undergo comprehensive functional screening at the biomechanics laboratory. Using a decision-making scheme, the identified functional deficits will be used to customize an individual rehabilitation plan. The rehabilitation plan will be conducted at the physical rehabilitation facilities of the institution by any of the 7 physical therapists working in the area (Additional file 1). Every professional attending the patients with shoulder complaints will be trained in and familiarized with the injury management model being implemented in the rehabilitation department. The training period will last for nearly 6 months, during which one of the authors ([name]) will explain and later supervise the successful application of the OCBRA at each component level. This training will take place during weekly meetings in which the therapist and the instructors will review every laboratory test, the rehabilitation prescription and the execution of the rehabilitative routines.

This study has been approved by the Clinical Research Ethics committee of the Public University of Navarra in accordance with the Declaration of Helsinki (the approval numbers for the clinical trials are Gov register: NCT02732002; PRS, protocols registration and results system). All the participants will be informed of the objectives and risks of the intervention. All the participants will sign an informed consent. The subjects’ names will be coded to preserve their anonymity.

The study decision-making scheme, i.e., the Objective Criteria Based Rehabilitation Algorithm (OCRBA), is presented in Table 1. For a clinically predominant pathology to be considered, at least 50% of the tests administered for each clinical entity must be positive. Every patient will be allocated to an injury type- and functional status-based rehabilitation program. During the rehabilitation process, the physical therapist will periodically evaluate the patient’s clinical status for stage progression during the procedure (Fig. 1). The criteria for periodical evaluation are based on the therapist’s subjective assessment of the patient’s progress over a 15-day period. Patients who do not progress to the next phase within 21 days will be referred to the laboratory for a biomechanical test. After 15 more days of the rehabilitation program in the same phase, another biomechanical test will be performed to evaluate whether the patient is making progress. If the patient does not improve by 25% between tests, the rehabilitation program will be considered ineffective, and the patient will be referred to the physician, who will propose other therapeutic modalities, such as joint corticoid infiltration or surgery (Fig. 1). This criterion is based on the empirical experience of the medical staff participating in the research and aims to avoid endless rehabilitation processes that reach a point of no return in the assistance chain and create economic burden for health care institutions. When the patient is clinically recovered, he or she will be referred by the physical therapist to the laboratory for a post-rehabilitation functional screening examination. Additionally, 50 patients recruited from the historical cohorts, will be recruited from the year before the OCBRA model is implemented to serve as controls. Concurrent randomization of patients is not possible in the present clinical research because every health institution has an ethical commitment to make the best effort to help patients recover from their illness.

**Table 1 Tab1:** Exercise prescription according clinical predominant pathology and patient’s functional status. Every test is performed recording isometric dynamometry (except for the GIRD). The rehabilitation staff prescribes an individualized exercises according to the functional status of the patient (column 3), determined by the functional tests performed in the biomechanical laboratory, and according to the clinical predominant pathology (column 2), determined by the medical staff and the functional tests

CLINICAL PREDOMINANT PATHOLOGY	ORTHOPEDIC TEST PERFORMED	PATHOLOGY RELATED EXERCISES (mandatory)	FUNCTIONAL STATUS EXERCISES (optional depending on patient’s functional status)
Rotator Cuff Pathology	Jobe test Patte test Gerber test	Glenohumeral instability exercises Scapulothoracic instability exercises	Strength deficit exercises Internal rotation deficit exercises
Scapular Dyskinesis	Scapular Retraction test Lateral Slide Scapular test	Scapulothoracic instability exercises	Glenohumeral instability exercises Strength deficit exercises Internal rotation deficit exercises
Impingement (micro-instability)	Howkins test O’Brien test Internal impingement test	Scapulothoracic instability exercises Strength deficit exercises	Strength deficit exercises Internal rotation deficit exercises
Instability	Apprehension test	Glenohumeral instability exercises	Scapulothoracic instability exercises Strength deficit exercises Internal rotation deficit exercises
Biceps-SLAP pathology	Speed test Upper cut test Biceps load test	Glenohumeral instability exercises Strength deficit exercises	Scapulothoracic instability exercises Internal rotation deficit exercises
GIRD	Sleeper test	Internal rotation deficit exercises	Glenohumeral instability exercises Scapulothoracic instability exercises Strength deficit exercises

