^2^ analysis. Following logarithmic transformation if required, mean changes in pain intensity, functional limitation (Simple Shoulder Test questionnaire), ROM and force application capability will be compared using a repeated measures paired *T*-Test. All analysis will be performed with SPSS^©^ (statistical software package for social sciences v 22.0 Chicago, IL, USA). The level of statistical significance will be set at *p* < 0.05. Simultaneously, the magnitude of the treatment effect will be tested by the determination of the effect size (Cohen’s *d*). This analysis will be performed as the standardized difference between two means (pre and post rehabilitation program). Cohen’s standard attributes and effect size for the intervention based on the magnitude of the observed size will be described as a large effect size for 0.8 or greater, medium for 0.5 to 0.8 and small for 0.2 or less [26].

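### The only examination called post-rehabilitation is triggered by clinical recovery, so the pre/post tests rest mainly on patients judged recovered and overstate the mean change for all OCBRA patients

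*Protocol article*

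**What the plan says.** All statements below are in the protocol article.

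- **Pre value.** *Study design and setting* measures every intervention patient at the start: "Before initiating the physiotherapeutic rehabilitation program, the patients will undergo comprehensive functional screening at the biomechanics laboratory".
- **Post value.** The same section ties the later examination to an outcome, not to a time: "When the patient is clinically recovered, he or she will be referred by the physical therapist to the laboratory for a post-rehabilitation functional screening".
- **Progress checks.** "The criteria for periodical evaluation are based on the therapist’s subjective assessment of the patient’s progress over a 15-day period". For slow progressors: "Patients who do not progress to the next phase within 21 days will be referred to the laboratory for a biomechanical test". After a further 15 days in the same phase, "another biomechanical test will be performed to evaluate whether the patient is making progress".
- **Ineffective programme.** If improvement between those two tests falls short of 25%, "the rehabilitation program will be considered ineffective, and the patient will be referred to the physician", who proposes other treatment. No post-rehabilitation examination is described for these patients.
- **Analysis.** *Statistics and sample size* describes an intra-group analysis of the patients recruited to the new model. Mean changes in pain, SST score, "ROM and force application capability will be compared using a repeated measures paired" t-test. On Cohen's d: "This analysis will be performed as the standardized difference between two means (pre and post rehabilitation program").
- **Reach.** Pain, range of motion and peak force are the primary outcomes and are laboratory measures. The SST is completed at the laboratory evaluations. The historical controls have no functional evaluation.

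**The concern.** A paired test needs a post value. The only value labelled as such is obtained once a therapist has judged the patient recovered, and that judgement is bound to correlate with change in pain, motion, force and self-reported function. Patients for whom the programme failed have a pre value but no designated post value. If the protocol is followed literally, entry to the comparison depends on something close to the outcome, and the mean change is biased upward.

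The stated aim is better functional capacity and symptom recovery among patients with shoulder injuries, not among those who recovered. All three primary outcomes and the SST are affected. Because controls are not measured functionally, no between-group contrast can reveal or offset the bias.

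**Working it through.** **The plan's own figures.** The plan gives no figure for this bias. Two of its numbers are used here. The first is 60 intervention patients. The second is the 0.05 significance level, whose sidedness is not stated. The sample-size constant of 7.9 fits a two-sided test: (1.960 + 0.842)² = 7.85. A two-sided 5% test gives a false improvement (significant and favourable) in 2.5% of trials when there is no bias.

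**Assumed inputs, not in the document.** The recovered share p is varied from 0.9 to 0.6. The correlation ρ between the recovery judgement and the change in an outcome is varied from 0.3 to 0.7.

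**Model.** In all enrolled patients the change has mean μ and SD 1. A post value exists only if a recovery score, correlated ρ with the change, passes the threshold a that a share p exceeds. With φ the normal density and λ = φ(a)/p:

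- mean change among those measured = μ + ρλ
- variance among those measured = 1 − ρ²λ(λ − a)
- d = mean / SD among those measured (that is, per SD of the change)

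**Worked case: μ = 0, p = 0.8, ρ = 0.5.** a = −0.842 and φ(a) = 0.280, so λ = 0.280/0.8 = 0.350. Mean = 0.5 × 0.350 = 0.175. Variance = 1 − 0.25 × 0.350 × (0.350 + 0.842) = 0.896, so SD = 0.946. d = 0.175/0.946 = 0.185, on 0.8 × 60 = 48 pairs.

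**No true change**, 4,000 simulated trials of 60 patients in each cell:

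| Recovered | Expected pairs | Mean observed d (ρ = 0.3 / 0.5 / 0.7) | False improvement (ρ = 0.3 / 0.5 / 0.7) |
|---|---|---|---|
| 90% | 54 | 0.06 / 0.10 / 0.15 | 6% / 11% / 18% |
| 80% | 48 | 0.11 / 0.19 / 0.28 | 11% / 24% / 46% |
| 70% | 42 | 0.16 / 0.27 / 0.41 | 16% / 39% / 72% |
| 60% | 36 | 0.20 / 0.35 / 0.54 | 21% / 51% / 87% |

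**True d of 0.5**, from the formulas, for ρ from 0.3 to 0.7: the observed d is 0.57–0.69 at 90% recovered, 0.62–0.84 at 80%, 0.66–0.98 at 70% and 0.71–1.12 at 60%. On the protocol's own scale, where 0.8 or more is large, a medium effect could be reported as large. With post values on all 60 patients, the expected d stays at 0.5.

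**The case against.** **Stalled patients are tested.** They go to the laboratory twice, and if those visits count as functional evaluations they also complete the SST. No sentence excludes them from the paired analysis, and the analysed group is described as those recruited, not those recovered. A reader might infer that patients declared ineffective have no later data and drop out of every pre/post comparison. The document does not say so. What stands is that these tests are described as progress checks, nothing names them as the post value, and nothing says they repeat the full set of measures.

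**Referral is not withdrawal.** The text does not say that referred patients leave the study. Fig. 1, which describes this pathway, could not be read here, and a fuller protocol or analysis plan may say more. That narrows the point. It does not remove it, because the recovery trigger for the post examination is fixed in this document and general missing-data wording would not undo it.

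**The tested patients are not all successes.** Full recovery also requires a negative last medical examination and a positive biomechanical evaluation, so some of those tested may still fail. It would go too far to say that the analysis runs only on successes or selects on the outcome itself. Selection is on a correlate of the outcome, which is why ρ is kept below 1 in the calculation.

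**The consequence has limits.** Uncontrolled pre/post tests could not establish comparative effectiveness even with complete data. The comparison with historical care uses time to recovery, visits and costs, which do not rest on this examination in the same way. Both points are right and confine the finding to the within-group analyses.

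**Conclusion.** The point holds for the within-group pre/post analyses. As written, the paired t-tests and Cohen's d rest mainly on patients judged recovered. They overstate the mean change for all patients given OCBRA and could show a significant improvement without a true one.

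It is tempting to say that an ineffective programme would show a significant improvement. The documents do not support that, because neither the recovered share nor the correlation is given. If nearly all patients recover, the bias is small: spurious d 0.06–0.15 at 90%. If many do not, it is serious: 0.20–0.54 at 60%. The direction follows from the text, given that recovery goes with favourable change. The size is a range under the stated assumptions, and no single cell of the table should be quoted as the expected bias.

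**What to change.** In *Statistics and sample size*, define the main pre/post analysis on all enrolled OCBRA patients:

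1. For those judged clinically recovered, use the post-rehabilitation examination.
2. For those whose programme is declared ineffective, use the last laboratory test already planned, the second progress test. State that this test records the same pain, range-of-motion, force and SST measures.
3. Include patients with no later test through a mixed model. That model assumes missingness at random, which is doubtful here, so add a sensitivity analysis for outcome-dependent missingness.
4. Report the proportion clinically recovered beside every pre/post result.
5. Keep the recovered-only paired test as supportive and label it as such.

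**Cost.** This is mostly wording, because the laboratory visits are already planned. If the progress test is currently a shorter examination, completing it adds some laboratory time. Post values will come at unequal times: the second progress test falls about 21 + 15 = 36 days into a phase, whereas the recovery examination has no fixed time. This should be stated. The reported effect will probably be smaller. The change concerns measurement and analysis only, and leaves the progression, referral and treatment rules as they are.

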**Fig. 1 Fig1:**
[figure not shown]
Multi-etiologic shoulder injury management model for rehabilitation algorithm description

Full recovery will be determined by negative results on the last medical examination (for both the patients in the OCBR group and the clinical cohorts serving as controls) and positive results on the biomechanical evaluation (only for the patients in the OCBR algorithm). As the clinical cohorts will not undergo functional evaluations, the time to full recovery and the number of physician and physiotherapy visits will be analyzed to compared the cost-effectiveness of the two injury management models (the proposed vs. previous typical care).

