### Trial status

The trial will start recruitment on January 2017. The trial will remain undecidedly open given that the present intervention program is the standard for shoulder injury care at the friendly society for work-related injuries management wherein the study is being performed. Once 100 patients are enrolled, a case- series retrospective study will be performed to compare the cost efficiency in terms of time duration, number of physical therapy and physician visits perceived and economical burden of the present shoulder injury management program vs. historical cohorts of patients receiving care at our institution.

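### Full recovery requires a passed laboratory evaluation in the OCBRA group only, so time to full recovery is not the same endpoint in the two groups being compared

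*Protocol article*

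**What the plan says.** The definition stands in the protocol article under Study design and setting, in the paragraph after Fig. 1. The shared part is: "Full recovery will be determined by negative results on the last medical examination", for OCBRA patients and historical controls alike. The second part is "positive results on the biomechanical evaluation (only for the patients in the OCBR algorithm").

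The next sentence gives the reason for the difference, "As the clinical cohorts will not undergo functional evaluations", and goes on to say that "the time to full recovery and the number of physician and physiotherapy visits will be analyzed" in order to compare the two models.

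Earlier in the same section, the laboratory test is placed at the end of rehabilitation: "When the patient is clinically recovered, he or she will be referred by the physical therapist to the laboratory for a post-rehabilitation functional screening examination".

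Trial status restates the comparison with historical cohorts as one "to compare the cost efficiency in terms of time duration, number of physical therapy and physician visits perceived and economical burden". The readable text nowhere limits the between-group time to the medical criterion that both groups share.

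**The concern.** A time-to-event comparison needs the same event in both groups. Here a control counts as recovered on a negative medical examination, while an OCBRA patient in the same clinical state does not count until the laboratory evaluation is also positive. An OCBRA patient who is medically negative but does not pass the laboratory test stays unrecovered, and an equivalent control is recovered.

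The time comparison bears on one of the article's main claims. The abstract's Discussion presents the model as a way to shorten the time to regain functional capacity, and the main Discussion speaks of hastening return to activity. A true saving in time could be hidden, or an equally good model could look slower, because of the definition alone.

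**Working it through.** **1. The definitions side by side.** For a given clinical course, let M be the time at which the medical criterion is met and B the time at which the biomechanical criterion is met.

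- Control: T = M.
- OCBRA: T = max(M, B), which is at least M.
- Extra time from the definition: max(0, B − M). It is never negative. It is zero only for patients whose laboratory criterion is met no later than the medical one.

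The direction follows from the text and needs no figures.

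**2. The plan's own sample-size figure.** Statistics and sample size gives n = (2/d²) × c per group, with P = 0.05, power 0.8 and c = 7.9.

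- Check of the constant: c = (1.960 + 0.842)² = 7.849 for a two-sided test, close to the stated 7.9.
- The article gives no value for d, so 60 per group cannot be reproduced forward. Solved backwards, d = √(2 × 7.9/60) = 0.513, with power 80.2%.

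The sample size was not derived for time to recovery. I use 0.513 SD below only as a benchmark effect.

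**3. What the asymmetry could do.** The documents give no SD of recovery time, no laboratory pass rate and no delay. The following are therefore assumptions: a constant mean delay of b SD in the OCBRA group, equal SDs, a comparison of two means, and a two-sided 5% normal approximation.

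- Standard error in SD units at 60 v 60: √(1/60 + 1/60) = 0.183.
- Rejection rate with no true difference: Φ(b/0.183 − 1.960) + Φ(−b/0.183 − 1.960).
- Power for a true benefit of 0.513 SD: Φ((0.513 − b)/0.183 − 1.960).

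Example for b = 0.1: 0.1/0.183 = 0.548. The rejection rate is Φ(−1.412) + Φ(−2.508) = 0.079 + 0.006 = 0.085.

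| Assumed delay b (SD) | Significant with no true difference | Power for a true benefit of 0.513 SD |
|---|---|---|
| 0 | 5% | 80% |
| 0.1 | 8.5% | 62% |
| 0.2 | 19.5% | 40% |
| 0.3 | 37.6% | 21% |

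Study design and setting elsewhere gives 50 historical controls. At 60 v 50, the rejection rates for 0.1, 0.2 and 0.3 SD are 8.2%, 18.1% and 34.7%, so the picture is the same.

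**4. Which analyses are touched.** Pain, range of motion and force are the primary outcomes, and the Statistics section analyses them before and after within the OCBRA group. They do not use the recovery definition. The formula in the Cost effectiveness analysis section is built from visits, missed work days and costs. Time to full recovery is named as a comparator in the paragraph after Fig. 1, and Trial status speaks only of time duration.

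**The case against.** The strongest points on the other side are these.

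- **The size is unknown.** A reader might take the 15-day interval in Study design and setting as the wait after a failed final laboratory test and turn the bias into days. The text does not support that. The interval belongs to patients who have not moved to the next phase and are tested again while still in that phase. The readable text gives no interval for a repeat of the post-rehabilitation test. This objection stands, and it is why the working uses assumed delays in SD units.
- **The order of events is not fixed.** The physical therapist refers the clinically recovered patient to the laboratory. The text does not say whether the physician's last examination comes before or after that test, and Fig. 1 is not shown. If the examination comes afterwards, the delay would act by postponing that examination. The direction is unchanged, but the remedy must cover this case.
- **The criterion belongs to the model under study.** Any visits or lost work it generates are real costs of OCBRA. A reader might want the shared endpoint applied to visits, missed days and costs as well. Stopping those counts at medical clearance would leave out real costs and favour OCBRA. This stands and limits the fix to time.
- **The article explains the asymmetry.** It says that controls have no functional evaluation. That accounts for the difference but does not remove it, because the same sentence goes on to use the affected endpoint as the comparator.
- **The bias cannot create a benefit for OCBRA.** That is true, but it can still hide one or show a false disadvantage.

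**Conclusion.** The concern holds for the between-group comparison of time to full recovery. As written, the endpoint differs between the groups, and taken alone the difference can only lengthen the OCBRA time.

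Its size cannot be computed from the documents. Delays of 0.1 to 0.3 SD would raise the rate of false differences from 5% to between 8.5% and 38% at 60 v 60. Those delays, and the comparison of means behind the figures, are assumptions.

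A reader might infer more, and the documents do not support it:

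- The trial's primary results are not affected, because they are within-group.
- The comparison with historical care as a whole is not shown to run against OCBRA, since other biases of a historical control may run either way.
- Visit counts and missed work days are not shown to be distorted. They would rise only if patients remain in care until the laboratory test is passed, which the text does not state, and such extra care would be a genuine cost.

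This is a definite flaw in one secondary comparison. It should be corrected before that comparison is analysed.

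**What to change.** **Change the definition used for the between-group time comparison.** Suggested wording:

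> For the comparison of time to recovery between the OCBRA group and the historical cohort, recovery is dated in both groups at the first medical examination with negative results. The same dating rule applies in both groups, and the date does not depend on the laboratory result. The biomechanical pass and its date are reported descriptively for the OCBRA group only. Visits, missed work days and costs are counted over the whole episode of care in both groups, including any that arise from the laboratory criterion.

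This concerns the analysis date only and changes nothing in how patients are managed. Using the first negative examination, independent of the laboratory, matters: a last examination held back until the test is passed would carry the delay into the shared endpoint.

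**Cost.** The change is mainly wording. Control recovery already rests on the medical examination, so the same source should supply its date. In the OCBRA group, the result and date of each medical examination must be recorded whatever the laboratory shows. The sample size does not change.

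**Downside.** The time endpoint no longer reflects functional recovery in the OCBRA group, which is then seen only in the separate descriptive report.
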